### Description of the ChildTalks+ meetings

#### Meeting 1

A therapist trained in the ChildTalks+ intervention conducts an initial meeting, if possible, with both parents/primary caregivers. If this is not possible, only the parent with mental health difficulties may be present. At the start, the therapist explains the purpose of the meeting and encourages the parents to view the mental disorder from the child’s perspective. The therapist talks to them about possible impact of the mental disorder on their children and family life and discusses with the parents possible protective factors for the family.

#### Meeting 2

Both parents should attend also the second meeting. The purpose of this meeting is to give parents advice and guidance on how to discuss the mental disorder at home. Different approaches can be taken for instance, a role play. At the end of the second meeting, the therapist and parents should prepare for the next meeting, in which the children will participate. Parents should indicate whether they prefer to conduct the conversation with their children themselves or whether they would prefer the therapist to do it. They work on the central themes that will require the most attention.

#### Meeting 3

Children should attend the third meeting together with their parents. One of the main goals of this session is to find out how the children are coping with the situation. The focus is on the children’s own experience of relationships with parents and peers. The parent or the therapist answer the children’s questions. The therapist tries to gain insight into the children’s coping strategies, strengths, and resilience. During this session, children should receive emotional support and sufficient, age-appropriate information about the parent’s mental disorder.

#### Meeting 4

The fourth and final meeting is held, if possible, with both parents and their children. Its purpose is to summarize and evaluate the previous meetings. The therapist answers the family’s questions and allows parents and children to express their perspectives. All this should help parents gain a better understanding of their children’s needs and to be better equipped to meet them. Subsequent steps are discussed with the family, including options for follow-up care [28, 64].

Figure 3 presents an overview of the Child Talks+ meetings [64]. The authors’ permission to publish has been obtained.

**Fig. 3 Fig3:**
[figure not shown]
Overview of the Child Talks+ meetings

### Intervention integrity

The manualization, training, and supervision carried out as part of ChildTalks+ should help ensure consistency and quality of program delivery. The training of therapists will take 2 days, follow clearly defined procedures, and be led by authors of the ChildTalks+ intervention. Trained therapists will have access to the manualized ChildTalks+ intervention procedures, including brochures on mental disorders for parents and children and information about particular mental disorders. Trained therapists will follow the intervention manual and complete standard checklists (logbook) for each session.

### Allocation into groups

Using a quasi-experimental design, each family will be assigned to a condition (intervention or control group) based on a paired matching. Allocation to a group will be based on the number of identified risk factors in the family [3]. These include mental disorder/comorbidities of the respondent, frequency of hospitalizations, diagnosis of a mental disorder of the other parent, eventually the child or children, absence of another caregiver, ignorance of the respondent’s diagnosis within the family, and low household income. Common demographic data (gender, age, highest educational attainment, the number of adults and children in the household) are also collected from respondents.

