## Methods/design

### Trial design

The current study is designed as quasi-experimental, pre–post controlled, paired design, with two conditions: an intervention group and a control group. Planning of the study protocol drew on the Model Protocol by the Arctic University of Norway [28]. Figure 2 shows the study design, including the recruitment, inclusion and exclusion criteria, group allocation, and assessments at baseline, post-test, and follow-up, as well as the measures used.

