### Study settings

Implementation and evaluation of the ChildTalks+ intervention will take place in the Czech Republic. Participation will be offered to professionals from healthcare, social, and educational institutions (especially pedagogical–psychological counselling centers), who will become ChildTalks+ therapists after completing the training. Trained therapists will then recruit families with children aged 6–18, where one or both parents have been formally diagnosed with a mental illness. In addition to a wide range of mental disorders, our clinical specialization will help us focus on families where a parent has been diagnosed with an eating disorder. The recruitment of respondents will run in three waves. New ChildTalks+ therapists will be trained in each wave.

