## Discussion

Given the prevalence and burden of transgenerational transmission of mental disorders in COPMI, it is imperative that effective evidence-based prevention interventions be identified and disseminated as a routine part of care for patients with mental illness who are parents and in care of their children. The vulnerable COPMI group struggles with lack of parents’ awareness of mental health issues and the parents are often not aware of the child’s perspective, i.e., the child’s experience of the situation. Issues of stigma can prevent parents from having relevant conversations. For children, it is important understand their parents’ behavior in relation to their mental disorder, while parents need to understand the impact of mental illness on their child’s behavior. Parents and children welcome having information relayed to them by a mental health professional. In the long term, we expect that the ChildTalks+ intervention will reduce emotional problems in COPMI and prevent (further) mental health problems from developing.

The aim of this study will be to introduce and pilot test the preventive ChildTalks+ intervention for children whose parents suffer from a mental disorder. The results should demonstrate the efficacy of the ChildTalks+ methodology, including its sustainability over time, and thereby contribute new knowledge regarding the risk and protective factors acting on COPMI. The results should also objectively describe feasibility of this prevention program that is based on working with children through their parents. Given our specialization on patients with eating disorders, we will address the effects and feasibility of the ChildTalks+ intervention especially with respect to children whose parents have eating disorders.

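### Matching on a risk-factor count cannot decide which family of a pair is treated, and no chance step is described, so the efficacy claim goes beyond what the allocation supports

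*Protocol article*

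**What the plan says.** Under Trial design the article states: "The current study is designed as quasi-experimental, pre–post controlled, paired design, with two conditions: an intervention group and a control group". Under Allocation into groups it repeats the quasi-experimental label and says that "each family will be assigned to a condition (intervention or control group) based on a paired matching". The only basis it names is the count: "Allocation to a group will be based on the number of identified risk factors in the family". The items counted include the respondent's disorder and comorbidities, hospitalisations, a diagnosis in the other parent or a child, absence of another caregiver, the family not knowing the diagnosis, and low income. The text shown gives no rule for which member of a pair receives the intervention.

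Families are recruited by the therapists who will treat them, and "The recruitment of respondents will run in three waves" (Study settings). Under Procedure the same therapists hand out and collect the questionnaires. Controls receive the programme after T3 (Control group).

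The Discussion nevertheless says: "The results should demonstrate the efficacy of the ChildTalks+ methodology, including its sustainability over time". Strengths and limitations also speaks of assessing efficacy. The limitations listed there are stigma, undiagnosed parents and the age limits for child questionnaires. Non-random allocation is not among them.

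**The concern.** Pairing and assignment are two separate steps. Matching on a count settles which two families form a pair. Two families matched on it are then tied, or nearly so, on the only allocation variable named, so something else must decide who is treated first and who waits until after T3. If that something is related to how a family would change over the next two months anyway, for example through readiness to engage or the present course of the illness, the difference in course is counted as an effect of ChildTalks+.

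The planned analysis does not repair this. The pair random effect absorbs what the two families have in common, not a systematic difference between the treated and the untreated member. Covariate adjustment reaches only what was measured. Equal counts do not balance the individual risk factors either, because the count adds unlike items. More pairs would make a biased estimate more precise without making it less biased.

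**Working it through.** **Inputs.** From Sample size and power calculation: a difference of 2.5 between groups in the T0–T1 change, SD 4.90, two-sided 5% paired t-test, power 0.80, 33 pairs. From Statistical methods: the contrasts T0–T1, T0–T2 and T0–T3, with Holm adjustment. Assumed here: the size of the tilt *b*, that is, how much more the treated family of a pair would have improved without any intervention. The article gives no figure for it, so a range is shown.

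**Step 1: the plan's own figure.** With λ = δ√n/SD, the power is the probability that a noncentral t variable with n − 1 degrees of freedom and noncentrality λ exceeds the critical value in absolute size.

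- n = 33: λ = 2.5 × √33 / 4.90 = 2.93, critical value 2.037, power 0.811.
- n = 32: power 0.798.

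So 33 is the smallest number of pairs that reaches 0.80. The stated figure reproduces if 4.90 is read as the SD of the within-pair difference.

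**Step 2: the same test with no true effect and a tilt b.** Put *b* in place of δ, so λ = b√33/4.90. The critical value is 2.037 at α = 0.05 and 2.526 at α = 0.05/3 = 0.0167. The latter is the first Holm step if Holm covers only the three time contrasts, which is an assumption.

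| Assumed tilt b (points) | λ | Rejection at 5% | Rejection at 1.67% |
|---|---|---|---|
| 0 | 0 | 5.0% | 1.7% |
| 0.5 | 0.59 | 8.8% | 3.5% |
| 1.0 | 1.17 | 20.6% | 10.2% |
| 1.25 (half the planned effect) | 1.47 | 29.6% | 16.0% |

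**Step 3: the other direction.** The tilt may also run against the intervention. With a true effect of 2.5 and a tilt of −1.25, the expected difference is 2.5 − 1.25 = 1.25. By the 1.25 row, the power at 5% would then be about 30% instead of the planned 81%.

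**Step 4: randomising within the same pairs.** δ, SD, n and the 1:1 ratio stay as in Step 1: 33 pairs, 66 families, power 0.811. With no allocation tilt the test keeps its 5% level. The added sample size is zero.

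**The case against.** The quasi-experimental label is open. It appears in the design and allocation sections, and the Discussion also calls the work a pilot test. A declared design is not an error, and the efficacy wording could be corrected without changing the allocation. This stands in part: it makes the weakness transparent, but it does not make the design carry an efficacy conclusion.

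Several stronger readings are tempting, and the documents do not support them.

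- **That therapists choose who goes first.** Therapists recruit, treat and administer questionnaires, but no sentence says that they allocate. Ties could be broken by enrolment order, by alternation or by a coordinator. Figure 2, said to include group allocation, is not shown. What can be said is that no chance element is described and that the label makes one unlikely.
- **That bias does enter and favours the intervention.** The outcome is within-subject change, so stable differences in level between families cancel. Only differences in course matter, and their size and direction are unknown.
- **That the false-positive rate is 30%.** That figure belongs to one assumed tilt in one unadjusted test at 5%. The plan has an adjusted mixed model with Holm correction, under which the same tilt gives about 16% at the first step, and a tilt of 0.5 gives only about 3.5%.
- **That families must also be paired within eating-disorder status and child age.** The Discussion does say "we will address the effects and feasibility of the ChildTalks+ intervention especially with respect to children whose parents have eating disorders", but the research questions for this group concern feasibility and modification, and the number of such families is not stated. With three equal waves (an assumption), 66/3 = 22 families split by diagnosis and two age bands leaves about 22/4 = 5.5 per cell before any match on the count. The gain is debatable, and the issue is separate from selection bias.

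**Conclusion.** The point holds as a mismatch between allocation and claim. The article describes non-random assignment within matched pairs, names no rule that could separate two matched families, promises to demonstrate efficacy, and leaves the allocation out of its limitations. Selection bias in the T0–T1 change can enter and cannot be removed by the planned model.

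Its size cannot be derived from the document. For assumed tilts of 0.5 to 1.25 points, the false-positive rate would be about 9% to 30% against a nominal 5%, or about 3.5% to 16% against 1.7% at a Holm first step. These figures rest on the assumed tilt, on 4.90 being the SD of the within-pair difference, on an unadjusted paired t-test standing in for the mixed model, and, for the second range, on Holm covering only the three time contrasts.

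**What to change.** For all pairs not yet allocated:

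1. Keep the matching on the risk-factor count.
2. Complete consent and T0 in both families of the pair.
3. Then assign intervention or control within the pair from a concealed, computer-generated list held by a coordinator who has no contact with the families.

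For pairs already allocated, state how the treated family was chosen, flag these pairs in the data, and report a sensitivity analysis restricted to the randomised pairs. The article reports retrospective registration, so such pairs may exist. Add non-random allocation to the limitations and, for the non-randomised pairs, replace the efficacy statement with wording about an estimated association.

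The cost is a protocol amendment, a randomisation list, and some waiting for a matched partner. The amendment has to reconcile that wait with the Abstract, where the intervention follows within two months of baseline, and with T1, which is timed from T0. The sample size, the 1:1 ratio, the paired power calculation, the pair-level model and delivery to controls after T3 do not change.

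Randomising within pairs deals only with who in a pair is treated. It does not cure bias from unblinded self-report or from differential attrition.

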### Sample size and power calculation

Power analysis was computed based on the Model Protocol by Reedtz et al [28] We hypothesized that the within-subject change of the outcome between T0 and T1 should differ by about 2.5 between the intervention and the control group, with a pooled SD of the scores app. 4.90. For the power analysis, a simple two-tailed paired t-test with significance level of 5% was used to get a power of 0.8 with an estimated sample size of 33 pairs. Trained therapists will offer participation to 80–88 families, thus allowing for some attrition. A total of 66 families will be assigned to the intervention (*N* = 33) or control (*N* = 33) group.

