**Methods:**

ChildTalks+ therapists (professionals from health, social, and educational facilities) will recruit 66 families where a parent is treated for a mental disorder and the family includes children aged 6–18. Paired allocation into an intervention group (*N* = 33) and a control group (*N* = 33) will be based on the number of risk factors identified in the family. Both groups will complete questionnaires at the baseline, post-test, and follow-up assessments after six and 12 months. The intervention group will receive the ChildTalks+ intervention within 2 months of the baseline assessment; the control group after the last assessment. Questionnaires will be completed by parents and children aged 12+ and, in two cases, 15+ years. Quantitative data will be supplemented with qualitative data from ChildTalks+ therapists working with patients with eating disorders.

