#### Control group (*N* = 33)

Two months after the baseline assessment (T0), post-test assessment (T1) should be performed at the same time as the T1 assessment of the intervention group. Parents and children have a follow-up assessment 6 months from T1 (T2) and 12 months from T1 (T3). After the T3 follow-up assessment, families will receive the ChildTalks+ intervention.

In the qualitative part of the research, we also explore the use of the ChildTalks+ intervention by professionals who treat patients diagnosed with eating disorders. We will gather these qualitative data using semi-structured interviews to explore the feasibility of ChildTalks+ intervention for patients with eating disorders and their offspring, and to describe the therapists’ experiences during the collaboration, including perceived obstacles and positives. The results should also inform us about what parents and children found helpful about the ChildTalks+ intervention. The qualitative data will be assessed by a thematic analysis [65].

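### The attrition allowance sits before assignment: the 66 families assigned are exactly the 33 pairs needed for 80% power at T1, with no margin for later loss

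*Protocol article*

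**What the plan says.** All the figures are in the protocol article, section Sample size and power calculation. The planning effect is stated as follows: "the within-subject change of the outcome between T0 and T1 should differ by about 2.5 between the intervention and the control group". The spread assumed for it is 4.90, described as a pooled SD. As to method, the article reports that "a simple two-tailed paired t-test with significance level of 5% was used". Its target, and the resulting number, are given as "to get a power of 0.8 with an estimated sample size of 33 pairs".

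The next sentence deals with loss: "Trained therapists will offer participation to 80–88 families, thus allowing for some attrition". The section then fixes the number allocated: "A total of 66 families will be assigned to the intervention". That sentence goes on to split the total equally between the two groups, 33 each. The abstract (Methods) gives the same total as the number recruited: therapists "will recruit 66 families where a parent is treated for a mental disorder and the family includes children aged 6–18".

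The sections on the two groups place T1 two months after T0, and T2 and T3 at 6 and 12 months after T1. Statistical methods specifies a linear mixed-effects model with nested random effects for pair and family.

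**The concern.** An allowance for attrition should leave the required number of analysable units after losses. Here the surplus lies between the families approached and the families assigned. Once 33 + 33 families are allocated it is used up, and the number in the study equals the number the calculation requires. A family that leaves between T0 and T1 is not covered, although the sentence says attrition has been allowed for.

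At stake is the 80% power for the immediate effect, the only comparison for which the article claims power. Pairing sharpens the problem, because in a paired t-test the loss of one family also removes its partner from the analysis.

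**Working it through.** **Inputs from the article.** Difference 2.5; SD 4.90; two-sided 5% paired t-test; target power 0.80; 33 pairs required; 66 families assigned; 80–88 offered participation.

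**Assumed, because the article gives no figure.** Family loss L by T1 of 5% to 25%, independent between partners; within-pair correlation ρ of the change scores between 0 and 0.5. The 4.90 is taken as the SD of the within-pair difference in change, since that is the use that reproduces 33.

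**1. Reproduce the stated figure.** Standardised effect d = 2.5/4.90 = 0.510. Power is P(|T| > t(0.975, n−1)), where T is noncentral t with n−1 degrees of freedom and noncentrality d√n. For n = 33, d√33 = 2.931 and the critical value is 2.037, so power is 0.811.

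| Complete pairs | Power |
|---|---|
| 33 | 0.811 |
| 32 | 0.798 |
| 31 | 0.785 |
| 30 | 0.771 |
| 28 | 0.740 |
| 26 | 0.706 |

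The smallest n with power of at least 0.80 is 33. The stated figure is correct and contains no inflation for dropout.

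**2. Locate the allowance.** 80 − 66 = 14 families, and 14/80 = 17.5%. 88 − 66 = 22 families, and 22/88 = 25%. This whole margin falls between offer and assignment. After assignment, 66 − 2 × 33 = 0.

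**3. Power after loss, complete pairs only.** Expected complete pairs = 33(1 − L)². For L = 10% this is 33 × 0.81 = 26.7.

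**4. Power after loss, unpaired families kept.** Expected unpaired families per group = 33L(1 − L). With a fixed pair-difference SD, generalised least squares gives an effective number of pairs of 33(1 − L)² + 33L(1 − L)(1 − ρ). For L = 10% this is 26.73 + 2.97 = 29.7 at ρ = 0, and 26.73 + 1.49 = 28.2 at ρ = 0.5. Degrees of freedom are taken as complete pairs plus unpaired families minus 2.

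| Family loss (assumed) | Complete pairs | Power, complete pairs only | Power, unpaired families kept (ρ = 0.5 to 0) |
|---|---|---|---|
| 5% | 29.8 | 0.77 | 0.78–0.79 |
| 10% | 26.7 | 0.72 | 0.75–0.77 |
| 15% | 23.8 | 0.67 | 0.71–0.74 |
| 20% | 21.1 | 0.61 | 0.67–0.72 |
| 25% | 18.6 | 0.55 | 0.63–0.69 |

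**5. The other reading of the 80–88.** If 80–88 were the number enrolled and assigned (40–44 pairs), power before any loss would be 0.88 to 0.91.

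**The case against.** Five points can be made for the plan.

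- **Small losses hardly matter.** This stands. Losing one pair gives 79.8%, which still rounds to the stated 0.8, and two give 78.5%. The shortfall passes two points only at the third lost pair. A reader might infer that any dropout breaks the design, and the figures do not support that.
- **The planned analysis is not a paired t-test.** This stands in part. The mixed model can use a family whose partner has left, so the complete-pair column overstates the cost. Power still falls below 0.80 at every loss rate in the table.
- **The claim concerns T1 only.** This stands. A reader might infer that the 80% requires full retention at T2 and T3 as well, but the article claims no power there, so later loss cannot contradict a stated figure. Nor should power under a Holm-adjusted level be charged to attrition: at 0.05/3, 33 pairs with no loss already give only 0.66, which is a matter of multiplicity.
- **The 17.5% and 25% are not dropout rates.** This stands. They are the gap between offer and assignment, and nothing in the article suggests losses of that size within two months. The article also names retention measures: reminders (Procedure), and full information before enrolment and help with questionnaires (Strengths and limitations).
- **An article condenses, and replacement rules may be in the full protocol.** This is fair, and their absence is not the point made here. The article does state an attrition allowance, but at a stage where it cannot serve that purpose.

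Offering participation might also have been meant as enrolling. The abstract and the sample size section both fix 66, so the text would still need correcting.

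**Conclusion.** The point holds as a misplaced allowance, not as an error in the calculation. The 33 pairs are correct for the stated test and inputs. The number assigned is that minimum, and the surplus described as covering attrition is spent before assignment.

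The size of the shortfall depends on a loss rate that the article does not give. At 10% family loss by T1, power would be about 0.72 on complete pairs, or 0.75 to 0.77 if unpaired families are kept. These figures rest on independent losses between partners, the assumed correlation range, and 4.90 as the SD of the pair difference. The degrees-of-freedom convention moves the mixed-model figures by only one or two points.

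It might also be inferred that T2 and T3 are to be analysed as separate two-time-point models that discard partial data. Statistical methods says only that they are assessed in the same way as T1, which is compatible with contrasts from one model, so no criticism of the model is made here.

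**What to change.** In Sample size and power calculation, describe the 80–88 families as an allowance for refusal or loss before assignment. If 80–88 is the number meant to be enrolled, say so and correct the 66 and the 33 per group there, in the abstract and in the group headings.

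Then restate T0–T1 power for the pairs expected at T1, over a stated and openly assumed range of loss, under the planned mixed model with its assumed within-pair correlation. Add that no power is claimed for T2 and T3, where cumulative loss can only be greater if dropout is permanent.

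The cost is a few sentences and one recalculation. The quoted power becomes slightly less favourable. No additional families are needed.
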